## Abstract

**Background:**

Breast cancer (BC) is a major public health issue. More than one out of five women treated for breast cancer will develop lymphedema in an upper extremity. Current evidence advocates transdisciplinary oncological rehabilitation. Therefore, research in this area is necessary since limited consensus having been reached with regard to the basic essential components of this rehabilitation.

Consensus has, however, been reached on the use of decongestive lymphedema therapy (DLT), but due to a lack of tests, the necessary dosages are unknown and its level is moderately strong.

This study attempts to verify both the efficacy of activity-oriented proprioceptive antiedema therapy (TAPA), as compared to conventional treatments such as DLT or Complex Physical Therapy (CPT), as well as its efficiency in terms of cost-effectiveness, for patients affected by breast cancer-related arm lymphedema.

**Methods:**

Controlled, randomized clinical trial with dual stratification, two parallel arms, longitudinal and single blind. 64 women with breast cancer-related arm lymphedema will take part in the study. The experimental group intervention will be the same for stage I and II, and will consist of neuro-dynamic exercises oriented to the activity, proprioceptive neuromuscular facilitation activities and proprioceptive anti-edema bandaging. The control group intervention, depending on the stage, will consist of preventive measures, skin care and exercise-prescribed training in the lymphedema workshop as well as compression garments (Stage I) or conservative Complex Decongestive Therapy treatment (skin care, multi-layer bandaging, manual lymphatic drainage and massage therapy) (Stage II).

**Results:**

Sociodemographic and clinical variables will be collected for the measurement of edema volume and ADL performance. Statistical analysis will be performed on intent to treat.

**Discussion:**

It has been recommended that patient training be added to DLT, as well as a re-designing of patient lifestyles and the promotion of health-related aspects. In addition, clinical trials should be undertaken to assess neural mobilization techniques and proprioceptive neuromuscular facilitation should be included in the therapy. Cohesive bandaging will also be performed as an early form of pressotherapy. The proposed study combines all of these aspects in order to increased comfort and promote the participation of individuals with lymphedema in everyday situations.

**Limitations:**

The authors have proposed the assessment of the experimental treatment for stages I and II. One possible limitation is the lack of awareness of whether or not this treatment would be effective for other stages as well as the concern for proper hand cleansing during use of bandages, given the current COVID-19 pandemic situation.

**Trial registration:**

This trial was registered in ClinicalTrials.gov (NCT03762044). Date of registration: 23 November 2018. Prospectively Registered.

## Background

Breast cancer (BC) is a major public health issue, being the most common global cause of cancer-related deaths in females and the second most common form of cancer, with over 2 million new cases occurring in 2018 [1]. BC survival rates have improved notably over the past 20 years (survival from this type of tumor increases by 1.4% annually) [2]. BC survivors face challenges in their activities of daily living (ADL), as a result of both the illness and the subsequent treatments undertaken. These challenges include altered sensory and pain functions and neuromusculoskeletal and movement-related alterations, as well as alterations of the skin and related structures. These symptoms tend to continue for extended periods of time and therefore, BC survival has been categorized as a chronic illness with new challenges arising for rehabilitation services [3, 4].

It is estimated that more than one out of every five women treated for BC will develop lymphedema in an upper extremity (20% in 6 months, 36% in 1 year and 54% within 36 months). The most relevant risk factors are the number of lymph nodes excised in surgery, radiation therapy and obesity. This is a chronic and progressive disorder that causes edema, skin changes (which may cause fibrosis and deformity), pain, sensitivity alterations, fatigue, limitations in joint rotation, recurrent infections, an inability to independently carry out ADL, low self-esteem, etc. Although it has been recognized for years now, consensual treatment dose programs have yet to be established [5].

Tertiary prevention in BC attempts to combat the consequences of this illness. It includes aspects such as rehabilitation, relapse prevention, early diagnosis of second malignancies, management of late complications through treatments and emotional support. This type of assistance has been traditionally presented for some time now in specialized health care, but it is currently becoming an increasing primary care responsibility [6, 7].

Rehabilitation of BC patients is intended to ensure their social integration and participation. Current evidence suggests the importance of transdisciplinary oncological rehabilitation. Therefore, research in this area is essential [8], since it is of great importance and quite different from the treatment phase and should include physical and occupational therapies (OT) [9]. Numerous rehabilitation models currently exist, but consensus has not been reached as to the basic necessary components of integral rehabilitation for cancer survivors [10, 11]. The regional government of Andalusia (Spain) designed an Integrated Palliative Care Process (IPC) for BC [12], which includes aspects to be carried out during the rehabilitation process, including lymphedema therapy, whose implementation has been quite disparate in the distinct provinces of the region. The literature also finds follow up recommendations based on risk factors and care level [7].

Consensus has been reached with regard to the utility of decongestive lymphedema therapy [13] but tests have yet to determine the optimal treatment dosage to be used and the level of evidence regarding its effectiveness in lymphedema treatment is only moderately strong, due to a limited number of randomized trials conducted with control groups, a lack of well-controlled interventions and measurements of precise volume, mobility or function and quality of life [5, 14, 15]. Similarly, the prescription of compression garments for lymphedema is quite varied and may be due to the lack of underlying evidence to inform on the treatment [16–18].

Evidence also suggests that complete and effective post-operative BC rehabilitation should also include patient self-control (empowerment), focus on the redesigning of their life style and include health promotion aspects [8, 19–21].

Studies have also confirmed that women with lymphedema and pain following BC may present alterations in their neuro-mechanical sensitivity [22] and neuropathic pain, as a result of nerve compression, or peripheral neuropathy induced by chemotherapy [2]. So, clinical trials should be carried out to assess neural mobilization techniques that focus on the functionality of the upper limbs [23], based on the clinical neural mobilization mechanism to reduce the intra-neural edema [24].

Studies have suggested the incorporation of proprioceptive neuromuscular facilitation elements (PNF) with traditional methods of manual lymphatic drainage (MLD), to facilitate the treatment process for lymphedema patients, since they induce powerful synergic effects on edema volume, range of motion (ROM) of the shoulder, pain and depression [25]. Their independent or combination use with laser treatment has also been suggested, since improvements were also found in these variables and even in the rate of blood circulation in the underarm [26]. Also, in a study in which bandaging was not used, CDT was combined with PNF and respiration, reducing the lymphedema and also improving ROM [27], which could potentially improve activity performance, participation level and thus, quality of life [14, 28].

In response to the evidence regarding the use of the Coban®3 M bandage as an early precursor to pressotherapy in the rehabilitating treatment of lymphedema to reduce prolonged edema (the causal agent of multiple complications and functional loss) [18, 29–31], we propose the possibility of testing the effectiveness of similar bandages, but ones that avoid compressive syndromes, decrease pain and edema, promote the development of ADL and improve the treatment’s cost-effectiveness [32, 33]. We suggest combining its use with the three previously mentioned techniques (healthcare education/patient training, neuro-dynamic activities geared to neuro-muscular use and proprioceptive neuro-muscular facilitation oriented towards ADL) and which, collectively, are referred to as “TAPA” (in Spanish, Activity-oriented proprioceptive antiedema therapy).

Given the consensus for conservative lymphedema treatment, such as Complex Decongestive Therapy (CDT) or Complex Physical Therapy (CPT), we believe that comparison with our TAPA treatment should be made with this type of treatment.

This study attempts to assess the effectiveness of TAPA, in terms of cost-effectiveness, calculating costs of material and human resources. Current expenditure on bandaging materials for CDT is at least double that which would be spent on TAPA, since, instead of multi-layers (usually two or three) only one is used here, and patients may require an annual prescription for compression garments, included in the catalogue of orthoprosthetic products of the Andalusian Health Service [34] and the use of these is minimized by TAPA. Personnel expenses for CDT are for approximately 60 min per treatment, using an individual approach formula, while TAPA sessions are approximately 30 min, and are carried out individually, with the possibility of a group approach. This, as well as the effectiveness of the treatment in terms of measurement of the reduced volume of the lymphedema, will improve the functionality of the upper extremity, during the performance of daily living activities (occupational) and therefore, in HRQOL.

## Hypotheses and objectives

Hypothesis: Activity-oriented proprioceptive antiedema therapy is more cost-effective than standard treatment.

### Objectives

This study aims to verify both the efficacy of the new therapy (TAPA) versus conventional treatment, as well as its efficiency in terms of cost-effectiveness, in patients suffering from Breast Cancer-Related Arm Lymphedema (BCRAL).

### Specific objectives

To measure the decrease in volume of the affected limb treated with TAPA and the maintenance of the effect over time (1 month and 3 months).To evaluate its effect on the performance of activities of daily living (ADL).To evaluate its effect on health-related quality of life (HRQOL).To determine efficiency in terms of simplicity of handling and economy of the anti-edema bandage technique used in the TAPA group.

## Methods

### Design

Controlled clinical trial, randomized by stratification in two gradients, with two parallel arms, longitudinal and single blind. To measure the efficiency of the new treatment, a cost-effectiveness study will be performed [34–36] .

### Study subjects

The study population will be females who were treated for breast cancer, diagnosed with Breast Cancer-Related Arm Lymphedema (BCRAL), referred to the UGC Rehabilitation Inter-levels of the Reina Sofía Hospital–Córdoba and Guadalquivir health district, from either the multi-disciplinary breast department of Specialized Care or the Primary Care teams, whose flow diagram of referrals to rehabilitation, both in-hospital and at home, for the treatment of post-mastectomy lymphedema and for individual or group treatment, is described in the Guide to Rehabilitation and Physical Therapy Procedures in Primary Care [37].

### Selection criteria

#### Inclusion criteria

Women, treated for BC with a diagnosis of level I and II BCRAL, according to stratification of the Work Group of the 11th International Congress of Lymphology [38], which establishes:

• Stage 1 or mild: difference in the circometry of less than 4 cm (in volume 10–25%) with respect to the healthy arm.

• Stage 2 or moderate: difference in the circometry of between 4 and 6 cm (in volume 25–50%) with respect to the healthy arm.
Patient’s informed consent.

#### Exclusion criteria

Health problems, illnesses or disabilities that prevent them from participating in the intervention.Other pathologies affecting the HRQOL: untreated cardiac, renal or respiratory insufficiency.Bi-lateral lymphedema.

#### Participant inclusion

Department specialist in rehabilitation invites the patient to participate, informing them of the purposes of the research and its procedures.

If they decide to participate, they should sign the Informed Consent, which shall be kept by the researcher.

Once the subject is included in the study, they will be assigned a study protocol number, which will serve to identify them in all of the study documents. This is a unique identification number created with an algorithm based on the center where they came from, their initials and date of birth, which shall subsequently be encrypted in an 8-digit number in the coordinating center. The codes shall be delivered to each researcher at the start of the study.

### Sample size

It is agreed that a decrease in the volume of the clinically relevant lymphedema may be established at 150 ml. (minimal detectable value) [39], 20% with respect to the baseline. Based on data from the literature on means and standard deviations [25, 40], for an alpha error of 0.05 and a statistical power of 0.80, the necessary sample size would be 29 subjects per group (calculation performed with EPIDAT 4.2). It is assumed that the standard treatment effect in the control group will lead to a reduction in arm volume by an average of 5%, the treatment effect in the experimental group will cause an average reduction in arm volume of 20%, and the standard deviation will be similar in both groups, approaching 20% [41]. Taking into account the dropout rate of 10% in each group, the corrected sample size is 64 patients, randomly assigned to two groups with 32 patients each.

### Randomization

Subjects were selected randomly using stratified random selection, in stages I or II, according to stratification of the Work Group of the 11th International Congress of Lymphology. Following capture and recruitment, participants were randomly assigned to one of the two groups **(experimental or control).**

### Random allocation and concealment of allocation

The random assignment sequence was created using EPIDAT, 3.1 statistical software, which stratifies the patients according to lymphedema stage, with a 1:1 ratio, using blocks having a random size of 4. The assignment sequence was hidden from the researcher assessing the participants through sequentially numbered envelopes that are opaque, sealed and stapled.

Allocation will be carried out by a department specialist in the Physical Medicine and Rehabilitation department.

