### Sampling technique

Consecutive sampling. Patients who comply with the selection criteria will be invited to participate in the study as they are identified and captured by the field researcher entrusted with this task.

Sampling will be carried out by a department specialist from the Physical Medicine and Rehabilitation department.

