### Blinding

Following the assignment of the interventions, these results will be hidden from the evaluator, who is a final year medical resident specializing in Physical Medicine and Rehabilitation (AJ), who will also monitor the data and data analysts (LA and J), who will not receive information on which of the treatments corresponds to the distinct data.

The party responsible for the random assignment and participant capture will inform the evaluator and the participants of the distinct dates of results assessment for each of them, and they will be reminded of the same and will have this information confirmed (or modified) via telephone on the preceding days.

Participants will attach the protocol follow-up sheet, registering any adverse effects, if occurring, as well as drop outs, losses and causes for the same.

Study revision by part of the research team is ongoing, through the use of the new technologies and a formal quarterly meeting.

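### Concealment is stated only for the assessing researcher, while one party recruits and allocates and the only block size given is four, so a recruiter could deduce part of the sequence

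*Protocol article*

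**What the plan says.** All references are to the Protocol article.

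- **Random allocation and concealment of allocation.** The list comes from statistical software "which stratifies the patients according to lymphedema stage, with a 1:1 ratio", "using blocks having a random size of 4". On concealment it says: "The assignment sequence was hidden from the researcher assessing the participants through sequentially numbered envelopes", which it describes as opaque, sealed and stapled. Nobody else is named as being kept from the sequence. It continues: "Allocation will be carried out by a department specialist in the Physical Medicine and Rehabilitation department".
- **Sampling technique.** "Sampling will be carried out by a department specialist from the Physical Medicine and Rehabilitation department". Participant inclusion likewise has a rehabilitation specialist invite the patient.
- **Blinding.** In arranging notice of assessment dates, it treats assignment and recruitment as one role: "The party responsible for the random assignment and participant capture will inform the evaluator and the participants". Only the evaluator and the data analysts are said to be kept unaware of treatment.
- **Design and Interventions.** The trial is called single blind. The arms look different: short occupational therapy sessions with cohesive bandaging, against compression garments (stage I) or longer decongestive therapy sessions (stage II).

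**The concern.** Concealment and blinding protect against different things. Concealment keeps the next assignment from the person who judges eligibility and invites the patient. Blinding keeps the assignment already made from the person who measures the outcome. Under the concealment heading, the article names only the researcher who assesses participants. Most naturally that is the evaluator, so what is described works as blinding.

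The envelopes are a real safeguard against reading a single assignment early. They do not stop deduction by someone who knows the earlier assignments and the block size. A party who both recruits and assigns will normally know the earlier assignments, and a single published block size supplies the rest.

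At stake is selection at entry. One exclusion criterion, on health problems that prevent participation, leaves room for judgement. Stage, which sets both the stratum and the control regimen, turns on a cut-off (4 cm, or 25% in volume) measured by tape, and Table 2 itself describes the resulting volume as approximate. With 64 patients, a few steered decisions could matter. Neither assessor blinding nor an intention-to-treat analysis removes that kind of bias.

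**Working it through.** The article gives no figure for predictability, so there is none to reproduce. The inputs are its 1:1 ratio, the block size of 4, the two stage strata and the total of 64. The guesser is assumed to know the block size and the past assignments in each stratum, and all blocks are assumed complete (64 / 4 = 16 blocks).

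**Assignments known with certainty.** A 1:1 block of four has six equally likely orders: AABB, ABAB, ABBA, BAAB, BABA, BBAA. That makes 6 × 4 = 24 positions.

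- 1st and 2nd positions: never determined.
- 3rd position: determined when the first two are alike (AABB, BBAA), in 2 of 6 orders.
- 4th position: determined in all 6 orders.

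Total: (2 + 6) / 24 = 8/24 = 33.3%. Of 64 patients: 64 × 1/3 = 21.3, about 21.

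**Best-guess success.** The rule is to guess the arm that is behind, and to toss a coin when the arms are level.

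| Position | Chance of a correct guess |
|---|---|
| 1st | 1/2 |
| 2nd | 2/3 |
| 3rd | (1/3)(1) + (2/3)(1/2) = 2/3 |
| 4th | 1 |

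Sum: 0.500 + 0.667 + 0.667 + 1.000 = 2.833 per block. 2.833 / 4 = 70.8%, or 64 × 0.708 = about 45 correct, against 32 by chance.

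**Effect of varying the block size.** Block sizes other than 4 are illustrative assumptions. Results for them come from 3000 simulated sequences of 64, with a guesser who knows which sizes are possible but not their order.

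| Blocks | Known with certainty | Best guess correct |
|---|---|---|
| 4 only (exact) | 33.3% | 70.8% |
| 4 and 6 mixed | about 6% | about 69% |
| 4, 6 and 8 mixed | about 2% | about 68% |

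The simulation ran each trial as one sequence instead of two stage strata, so its figures are approximate. Varying the size removes most certain knowledge but barely lowers the guess rate. The remaining exposure comes from the recruiter knowing past assignments, so who releases each assignment matters more than the block sizes.

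**The case against.** Several points on the other side have weight.

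- **The envelopes are good ones.** They are numbered in order, opaque, sealed and stapled, and the Randomization section places assignment after recruitment. A reader might infer that there is no real concealment; the text does not support that. What stands is that such envelopes do not prevent deduction from earlier assignments.
- **The person assessing participants could be assessing eligibility.** The wording allows it. However, the Blinding section keeps the evaluator apart from the recruiting and assigning party, which makes outcome assessment the natural reading.
- **The dual role is not beyond doubt.** Sampling technique also mentions a field researcher who captures patients, and a specialist from the same department need not be the same individual each time. A reader might infer that the recruiter opens the envelopes and knows every earlier assignment; the article never says who opens them. The dual role rests mainly on one phrase about assessment dates, but that phrase is explicit and singular.
- **Fixed blocks are also a reading.** The phrase may be a poor translation of randomly permuted blocks of four, or of varying sizes. What can be said is that it contradicts itself and that four is the only size given.
- **The design is not described as open-label.** It is single blind, with evaluator and analysts blinded. The exact statement is that participants, therapists and the allocating party are not said to be blinded.
- **There are counterweights.** Sampling is consecutive and stage has numeric limits. These narrow the room for steering but do not close it.

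**Conclusion.** The point holds in a limited form. As written, the plan does not state that the sequence is concealed from the recruiter, it refers to one party for assignment and recruitment, and it gives a single block size in self-contradictory words. If blocks are fixed at four, up to 33% of assignments (about 21 of 64) could be known in advance and up to 71% guessed correctly.

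Both figures are ceilings. They need a recruiter who knows the block size and follows assignments by stage, and complete blocks in both strata. No section says the recruiter was told the block size. A reader might infer that selection bias has occurred; the article offers no evidence of that. What it shows is an avoidable exposure that should be reduced or, failing that, declared.

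**What to change.** 1. Reconcile the block wording: say whether the size is fixed at four or varies.
2. For patients still to be randomised, use block sizes that truly vary (for example 4 and 6 in random order) and do not disclose them to the recruiter. This alone is a partial remedy, as the table above shows.
3. Have the envelopes held and opened by an existing team member who neither recruits nor assesses outcomes, and only after consent, stage and baseline measurements are recorded. The coordinating centre could do this instead, but under Participant inclusion it only encrypts identification codes, so releasing assignments would be a new task for it.
4. State that concealment applies to the recruiting specialist.

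The cost is a new list for the remaining patients, a small logistic step at each enrolment, and slightly larger possible imbalance within stage. A recruiter who later sees the treatments given can still guess better than chance, so the exposure is reduced and not abolished.

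The article mixes past and future tense on randomisation, so it is unclear how far enrolment has gone. If recruitment has ended, report the block size used and the dual role as a limitation.
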